### Assessments

Physician screening was completed initially, followed by an MRI scan. If subjects were eligible following their MRI scan, the remainder of the baseline physical performance testing was completed. Subjects were randomized at the completion of all baseline assessments.

### Primary Outcome: Cartilage Thickness

A 3Tesla MRI scan (Philips Medical Systems, Achieva 3T) of the knee with the most severe clinical signs and symptoms was conducted at the Symbion Clinical Research Imaging Centre at baseline and following the 6-month intervention. OA cartilage morphology assessed via MRI is a reliable and valid technique, particularly for clinical trials where cartilage structure modification is an outcome [35,36]. Depending on the size of the participant's knee, either a SENSE Knee coil (smaller knee) or a SENSE Flex-L coil (larger knee) was used. The same coil was used for pre and post scanning. Prior to the commencement of the scan, a bead was placed on the thigh, halfway between the inguinal groove and the proximal margin of the patella measured anthropometrically by the same observer (AL) in all participants; this marker identified the area for the cross sectional image of the thigh region. The scans included a 3-Dimensional image T1 weighted gradient echo sequence of the tibiofemoral joint (repetition time = 34 ms, echo time = 9 ms, acquisition time = 9 min, flip angle = 25°, slice thickness = 1.4 mm, in-plane resolution = 0.31 mm), and a spin echo sequence of a cross-sectional slice of the thigh region (repetition time = 450 ms, echo time = 10 ms, acquisition time = 2 min, flip angle = 90°, slice thickness = 10 mm, in-plane resolution = 0.47 mm).

Blinded measurement of cartilage morphology involved the segmentation of articular cartilage in the medial and lateral tibia, and the central portion of the medial and lateral femur. Any cartilage or bone associated with osteophytes was excluded from segmentation. Chondrometrics software (see Figure 2) (Chondrometrics, Ainring, Germany) was used to segment the cartilage (coefficient of variation (CV) for cartilage thickness: medial tibia = 2.2%, lateral tibia = 2.1%, medial femur = 2.2%, lateral femur = 1.8%; cartilage volume: medial tibia = 3.2%, lateral tibia = 2.3%, medial femur = 3.9%, lateral femur = 1.6%). Datasets were analyzed in pairs, and the person responsible for segmenting each scan (AL) was blinded to the participants ID number and the timepoint of the scan. Quality control of all segmentations was performed by a single person (BV), reviewing all segmented slices of each data set. In addition, automatic quality control procedures were used to exclude mislabelling of medial versus lateral cartilage plates, tibial versus femoral cartilage plates and cartilage versus total subchondral bone contours, the software checking the distance vectors between different plates/contours and a fibular marking. Following cartilage segmentation, computations performed by Chondrometrics software provided outputs for medial and lateral tibial and femoral total subchondral bone area; denuded area (area of subchondral bone eroded, full thickness defect); mean thickness (mean cartilage thickness over total subchondral bone area), thickness covered (mean cartilage thickness over cartilage-covered subchondral bone area), cartilage volume, and VCtAB (volume of cartilage divided by total subchondral bone area).

**Figure 2 F2:**
[figure not shown]
**Part A: Sagittal view of right knee, arrows pointing to segmented (colored areas) areas of tibial cartilage (Medial = right-hand side, Lateral = left-hand side) using Chondrometrics software**. Part B: Medial (blue) and lateral (green) joint surface areas representing the tibial bone covered with articular cartilage.

The outputs for each compartment were analyzed separately; and compartments were also combined, i.e. total tibial cartilage volume (medial + lateral) =

$$\frac{\text{(Total tibial volume at baseline}-\text{Total tibial volume at 6 months})}{\text{Total tibial volume at baseline}}\times 100$$

The same equation applied for total femoral cartilage volume. Total medial compartment volume (medial femoral volume plus the medial tibial volume) was calculated, and the same equation applied for the total lateral compartment volume.

In addition to total compartment analysis, participants were categorized into both geographical OA (medial, lateral, or bi-compartmental) and also, the least and most affected compartment based on MRI Grade classification and osteophytes.

Image J software (Image J software v 1.37, Wayne Rasband, ) was used to calculate muscle and fat volume by a single blinded assessor (CV muscle = 0.16%, fat = 0.2%).

Two blinded physician assessors conducted baseline clinical musculoskeletal system evaluation and MRI interpretation (OA graded according to the MRI correlation of the Modified Outerbridge Classification 1961) at baseline and 6 months independently of each other.

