**Methods:**

Our cohort consisted of women over 40 years of age with primary knee osteoarthritis, according to the American College of Rheumatology clinical criteria. Primary outcome was blinded measurement of cartilage morphology via magnetic resonance imaging scan of the tibiofemoral joint. Secondary outcomes included walking endurance, balance, muscle strength, endurance, power, and velocity, body composition, pain, disability, depressive symptoms, and quality of life.

Participants were randomized into a supervised progressive resistance training or sham-exercise group. The progressive resistance training group trained muscles around the hip and knee at 80% of their peak strength and progressed 3% per session, 3 days per week for 6 months. The sham-exercise group completed all exercises except hip adduction, but without added resistance or progression. Outcomes were repeated at 3 and 6 months, except for the magnetic resonance imaging scan, which was only repeated at 6 months.

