### Blinding

All participants were blinded to the investigators' hypothesis as to which was the preferred group. Analysis of the primary outcome (MRI scan of cartilage morphology) was double-blinded at all time points. All baseline and follow-up physical performance and self-report assessments were performed double-blinded; except for follow-up physical performance testing, which was single blinded (participant only). At the final assessment, participants were required to fill-out a Completion Questionnaire without the assessor present. This questionnaire assessed the participants' perception of whether they felt they had been in the "preferred group" to "modify cartilage, increase muscle mass and strength, reduce pain, and improve physical function".

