### Sample Size

Reginster and colleagues [53] conducted an RCT of glucosamine vs. placebo in patients with OA, and reported no loss in joint space width (mean -0.06 mm) in the glucosamine group vs. a -0.31 mm joint space loss in the placebo group (p = 0.043). Radiographic joint space loss has been shown to be closely related to reduction in cartilage thickness by MRI, our primary outcome [54]. We conservatively assumed, given the lack of published data, that the protective effect of PRT would be 20% less than that of glucosamine (i.e. 80% rather than 100% reduction in cartilage loss). Therefore, our sample size was estimated from the expected rate of cartilage thinning in sedentary patients with OA of -2.8 ± 2.7% per 6 months [55], which we hypothesized would be unchanged by sham exercise in the controls but would be reduced by 80% to -0.56 ± 2.7% by PRT exercise. The sample size was inflated by 20% to accommodate the anticipated dropout rate over 6 months, based on previous exercise and OA trials in the literature and in our experience. Therefore, the final sample size targeted was 63.

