### Statistical analysis

Data were inspected for normality visually and statistically (skewness -1 ≥ 1), and expressed as mean and standard deviation or median and range, as appropriate. Non-normally distributed data were log-transformed prior to use with parametric statistics if possible or used with non-parametric tests if assumptions of normality were not met despite transformation. Our primary analytic strategy was a complete case analysis because of the novelty of our primary outcome. Our secondary sensitivity analysis was intention-to-treat with data imputed via the expectation maximization algorithm (covariates included in the model were group, baseline score, and compliance). Comparisons between groups were made using repeated measures analysis of co-variance (ANCOVA) for both time and group × time interactions, and ANCOVA models for % change scores adjusted for baseline value of each outcome for normally distributed continuous data. Additional covariates considered for inclusion in these models were characteristics at baseline which were different between groups and related to the dependent variable of interest. The Kruskal-Wallace test or Mann-Whitney U test were used for non-normally distributed continuous data. SPSS (Release 13.0 for Windows, 2004, Chicago: SPSS Inc) was used for all data analysis. All *P *values of less than 0.05 were considered statistically significant except for post-hoc comparisons of pairs of variables from significant Kruskal-Wallace models, which were adjusted for multiple comparisons using the method of Bonferroni. Clinical meaningfulness of differences observed was assessed by evaluation of the magnitude of the differences relative to clinical outcomes in the literature, and calculations of effect sizes (Formula 1) adjusted via Hedges bias-corrected effect size for small sample sizes [56]. Effect sizes were interpreted according to Cohen's interpretation of 'trivial' ( < 0.20), 'small' (≥ 0.20 < 0.50), 'moderate' (≥ 0.50 < 0.80), and 'large' (≥ 0.80) effect size [56]. Caution was taken when using Cohen's interpretations as these were originally based on psychological studies. 95% confidence intervals (CIs) for the relative ES were calculated.

$$\begin{array}{cc} \text{Effect Size}=\frac{\Delta \text{ Treatment}-\Delta \text{ Control}}{\text{Pooled SD}} & \left(\text{Formula }1;(56)\right) \end{array}$$

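### The primary outcome is named inconsistently and not fixed to one plate, output, combination or model, while testing runs at an unadjusted 0.05

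*Protocol article*

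**What the plan says.** **Name of the primary outcome.** The Abstract states: "Primary outcome was blinded measurement of cartilage morphology via magnetic resonance imaging scan of the tibiofemoral joint". Blinding agrees: "Analysis of the primary outcome (MRI scan of cartilage morphology) was double-blinded at all time points". The outcome section, however, is headed "Primary Outcome: Cartilage Thickness", and Sample Size says: "Radiographic joint space loss has been shown to be closely related to reduction in cartilage thickness by MRI, our primary outcome".

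**What is measured and analysed.** Under the primary-outcome heading, the blinded reading covers "segmentation of articular cartilage in the medial and lateral tibia, and the central portion of the medial and lateral femur", which is four plates. The software returns six outputs for each: total subchondral bone area, denuded area, mean thickness over total bone area, thickness over cartilage-covered bone, volume, and volume divided by total bone area (VCtAB). The text after Figure 2 adds: "The outputs for each compartment were analyzed separately; and compartments were also combined". The combinations it defines are volumes: total tibial, total femoral, total medial and total lateral. It also classifies participants by location of disease and by most and least affected compartment.

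**How it is tested.** Statistical analysis gives repeated-measures ANCOVA and ANCOVA of percentage change adjusted for baseline, without ranking them. Data that stay non-normal after transformation go to non-parametric tests. On the threshold, P "values of less than 0.05 were considered statistically significant except for post-hoc comparisons of pairs of variables" following a significant Kruskal-Wallis test; only those pairs receive a Bonferroni adjustment.

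**The concern.** A confirmatory claim needs one variable, or a small family with controlled error, fixed before the data are seen. Here the two names point to families of different size, and neither reduces to a single test. Cartilage thickness still leaves open which plate or combination, which of two thickness definitions, and which model. Cartilage morphology takes in nearly everything the software produces.

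The choice can change the answer. Thickness over cartilage-covered bone can rise when thin areas become denuded, while mean thickness over total bone area falls.

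The Discussion says the trial will give the first evidence that progressive resistance training (PRT) modifies the disease, and the Background says that publishing the methods first limits publication bias. Both aims weaken if any significant plate, output or model can be presented as the primary result.

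**Working it through.** **1. The plan's own figure.** Sample Size works from one comparison: −2.8% against −0.56% with SD 2.7%, a difference of 2.24, so d = 2.24/2.7 = 0.83. Power and sidedness are not stated, so the total of 63 cannot be reproduced without guessing. Two-sided 5% with 80% power gives 46–48 evaluable participants and 56–60 after the dropout allowance. One-sided 5% with 90% power can give exactly 63 (50/0.8 = 62.5). On any of these the trial is sized for a single test, with no allowance for several. With 20% dropout and equal arms (assumed), 63 × 0.8/2 gives about 25 completers per arm.

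**2. Count of variables.**
- All MRI measures: 6 outputs × 4 plates + 4 combined volumes = 28. Four of these are bone areas.
- Thickness, both definitions: 2 × 4 = 8.
- Mean thickness over total bone area only: 4.

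**3. Chance of at least one P < 0.05 with no true effect.** For m independent tests it is 1 − 0.95^m. For correlated tests it was simulated in two ways. One gives all tests the same correlation. The other is structured: 0.6–0.9 within a plate and 0.1–0.5 between plates, with the totals formed from the plate volumes. All correlations are assumptions.

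| Family | Independent | Common correlation 0.5 | Common correlation 0.9 | Structured |
|---|---|---|---|---|
| 4 | 18.5% | 15.5% | 9.3% | 16–18% |
| 8 | 33.7% | 25% | 12% | 21–30% |
| 28 | 76.2% | 49% | 17% | 31–57% |

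The headline ranges run from the lowest structured value to independence: 16–34% for thickness (4 or 8 variables) and 31–76% for all 28. A common correlation of 0.9 even between different plates would bring the figures lower, but still above 5%.

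**4. Direction.** These rates count effects either way. For a false positive favouring PRT, 28 measures give 51% if independent and 15–32% in the structured simulation.

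**5. The second model.** In 20,000 simulated null trials (25 per arm, assumed baseline CV 15%), a test on absolute change, equivalent to the group × time test, rejected in 4.9%. ANCOVA of percentage change rejected in 5.0%, and one or the other in 6.0%. The number of measures drives the error; the second model adds about one percentage point per variable.

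**6. The one adjustment stated.** Pairwise comparisons after Kruskal-Wallis need three or more groups. The trial has two, so this adjustment leaves the primary comparison untouched.

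**7. Power with each remedy** (d = 0.83, 25 per arm, two-sided t test): 82% for one test at 0.05, and 73% at 0.025, the first Holm step for two tests. Bonferroni gives 63% over 4 tests, 53% over 8 and 37% over 28.

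**The case against.** A condensed article may leave endpoint hierarchy to an analysis plan that is not shown, and two places do name thickness. The first argument carries some weight, but the article does not stay silent: it states a threshold for all tests with one exception, and says the compartment outputs were analysed separately. That is a rule fixed badly rather than a detail left out. The second narrows the family to 8 or 4 variables but does not bring it to one.

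Some stronger readings are tempting and not supported:

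- **A reader might infer that 28 primary endpoints are declared.** They are not. Twenty-eight counts the MRI measures analysed under the heading, and four of them are not cartilage. The compartment classifications are described as ways of grouping participants, not as primary tests.
- **A reader might infer that a false claim of disease modification is more likely than not.** Among the scenarios run, the chance of a false positive favouring PRT passes one half only for 28 independent tests (51%), and the definitions rule independence out. VCtAB is close to mean thickness over the same area, and the totals are sums of plate volumes.
- **A reader might infer that two models double the error.** They overlap heavily, and percentage-change ANCOVA is specified only for normally distributed data.
- **A reader might use the reported measurement CVs ("coefficient of variation (CV) for cartilage thickness: medial tibia = 2.2%, lateral tibia = 2.1%, medial femur = 2.2%, lateral femur = 1.8"%) to argue that reading error alone exceeds the planned SD of 2.7%.** The article does not say whether the CVs come from repeat scans or repeat segmentation, nor which plate the 2.7% describes, and scans were read in pairs. That is a separate question of precision, and nothing here depends on it.

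**Conclusion.** The point holds. The primary outcome has two names and is not reduced to one plate, output, combination or model, and the stated significance rule gives no protection across the candidates. Error exceeded 5% for every family and correlation tried. The 16–34% and 31–76% ranges are indicative: they depend on which reading is taken and on correlations the document does not supply. The inconsistency and the lack of a single primary test depend on no assumption. It should be corrected before unblinding, because the disease-modification claim rests on this outcome.

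**What to change.** Before unblinding, name one output, mean cartilage thickness over total subchondral bone area in the study knee at 6 months, and one model, ANCOVA adjusted for baseline. Then choose one of two structures:

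- **One combined thickness** tested at 0.05. The plates included and the way they are combined must be written down, because the article defines combinations only for volume.
- **Total tibial and total femoral thickness**, the two sites named in the hypothesis, tested with Holm at 0.05.

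Use the same name for the outcome in the Abstract, Blinding, the primary-outcome section and Sample Size. Label as secondary or exploratory, without an efficacy claim, the separate plates, volumes, VCtAB, denuded area, thickness over covered bone and bone area. Do the same for the analyses by most or least affected compartment and by medial, lateral or bi-compartmental disease.

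The cost is wording. A lone significant plate or output can no longer be called the primary result. Holm over two sites costs some power: 73% for a given site at its first step against 82% for a single test, under the plan's own effect size. Averaging over compartments could also dilute an effect confined to one of them, so the choice of combination should be argued, not defaulted.

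### The four combined cartilage measures use volume only, although thickness is the outcome named and sized and, by the article's own CVs, is less noisy for three of the four combinations

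*Protocol article*

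**What the plan says.** The article's primary-outcome section is headed "Primary Outcome: Cartilage Thickness", and the Sample Size section repeats the choice: "reduction in cartilage thickness by MRI, our primary outcome". The sizing inputs are also per cent thinning. The control arm has an "expected rate of cartilage thinning in sedentary patients with OA of -2.8 ± 2.7% per 6 months", and under training this "would be reduced by 80% to -0.56 ± 2.7% by PRT exercise".

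Within the primary-outcome section, the text after Figure 2 says that each compartment's outputs are analysed separately and then adds pooled measures: "compartments were also combined, i.e. total tibial cartilage volume (medial + lateral"). The formula shown is per cent change in total volume. The same formula is applied to the femur, to the medial compartment and to the lateral compartment. No pooled thickness is defined.

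The same section gives reading CVs for both quantities by plate:
- The first list is "cartilage thickness: medial tibia = 2.2%, lateral tibia = 2.1%, medial femur = 2.2%, lateral femur = 1.8" (all values in per cent).
- The second list, on the same four plates and in the same unit, is "cartilage volume: medial tibia = 3.2%, lateral tibia = 2.3%, medial femur = 3.9%, lateral femur = 1.6".

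It also lists mean thickness over total subchondral bone area, and that bone area, among the software outputs for each plate.

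**The concern.** Pooling two plates averages out part of the reading error, so pooled measures can be the most precise cartilage comparisons in the trial. The article takes this gain only on volume. On three of the four plates volume has the larger CV, and the gap is widest on the two medial plates. The pooled results are therefore not on the quantity used for sizing, and three of them carry more measurement error than they need to. At stake is the precision of the medial, total femoral and total tibial comparisons.

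**Working it through.** **1. The plan's own figure.** The Sample Size section targets 63 and gives neither power nor sidedness, so 63 has no unique derivation. The difference is 2.8 − 0.56 = 2.24 points, with SD 2.7. By the normal approximation, n per arm = 2(z₁₋α/₂ + z₁₋β)²(2.7/2.24)². Two-sided 5% and 85% power give 26.09 per arm, and 2 × 26.09 × 1.2 = 62.6, i.e. 63. One-sided 90% gives 50/0.8 = 62.5, also 63. So 63 can be reached, but only with an assumed power. After 20% dropout, 63 × 0.8 ≈ 50 women remain, or 25 per arm. A two-sided t-test then has 82% power for 2.24 points at SD 2.7. This is the reference below.

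**2. Error of a pooled measure.** For plates with CVs a and b and weight w on the first, pooled CV = √[(wa)² + ((1−w)b)²], assuming independent plate errors. With w = 0.5 this is √(a² + b²)/2. For example, medial volume is √(3.2² + 3.9²)/2 = 2.52, and medial thickness is √(2.2² + 2.2²)/2 = 1.56. If the errors of the two scans are independent, the error in a per cent change is √2 times the pooled CV.

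| Combination | Pooled CV, thickness | Pooled CV, volume | Ratio | Change error, thickness | Change error, volume |
|---|---|---|---|---|---|
| Medial | 1.56 | 2.52 | 1.6 | 2.2 | 3.6 |
| Femoral | 1.42 | 2.11 | 1.5 | 2.0 | 3.0 |
| Tibial | 1.52 | 1.97 | 1.3 | 2.15 | 2.8 |
| Lateral | 1.38 | 1.40 | 1.0 | 2.0 | 2.0 |

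**3. Is the direction robust?** With independent plate errors, volume is noisier at every weighting for the medial and tibial combinations. For the femoral one it is noisier unless the medial femur carries less than about 20% of the weight. With weights from 0.4 to 0.6 the ordering for these three also holds with plate-error correlation up to 1. The lateral combination moves slightly either way (the lateral femur CV is 1.6 for volume and 1.8 for thickness).

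**4. Power.** All scenarios use a difference of 2.24 points, 25 per arm, a two-sided 5% t-test, equal weights, independent plate errors, and the same per cent effect on volume and thickness. Let ρ be the assumed correlation of reading error between a woman's two scans, so that change error e = CV × √[2(1−ρ)].
- Case A: the 2.7 already contains the thickness error. Volume SD = √(2.7² − e_th² + e_vol²).
- Case B: error adds to the 2.7. SD = √(2.7² + e²) for each measure.

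Worked example, medial, case A, ρ = 0: √(2.7² − 2.20² + 3.57²) = 3.90, and power is 51%.

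Power, thickness → volume (%):

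| Case, ρ | Medial | Femoral | Tibial |
|---|---|---|---|
| A, 0 | 82 → 51 | 82 → 61 | 82 → 67 |
| A, 0.5 | 82 → 64 | 82 → 70 | 82 → 74 |
| A, 0.75 | 82 → 72 | 82 → 76 | 82 → 78 |
| B, 0 | 61 → 41 | 64 → 49 | 61 → 52 |
| B, 0.75 | 76 → 67 | 77 → 71 | 76 → 72 |

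From unrounded values the loss runs from 8.9 to 30.7 points (medial), 5.7 to 21.4 (femoral) and 3.7 to 14.9 (tibial). The lateral change is under 1 point throughout. These are scenarios, not bounds. For example, positive correlation of error between plates (0.5, case A, ρ = 0) takes medial volume power to 43%.

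**The case against.** The strongest reply is that nothing the trial was sized on loses power. The pooled volumes come in addition to separate plate-level analyses, which include mean thickness, and the sample size does not rest on any pooled measure. That stands. A reader might infer that the trial's primary comparison falls from 82% to 51% power. The article does not support this: 51% is one scenario, for one additional measure.

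A reader might also conclude that volume is simply the wrong output. That goes too far. The abstract and the Blinding section describe the primary outcome as cartilage morphology, which includes volume, and summing volumes is a natural way to pool plates.

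The noise model also has a difficulty. With ρ = 0, thickness change on a single medial plate has error √2 × 2.2 = 3.1%, which already exceeds the planning SD of 2.7%. So it cannot be held against volume alone that its error exceeds 2.7%. Either the CVs are not independent per-scan errors, or 2.7% does not describe these readings. Scans were read in pairs, so some error may cancel, and the article does not say how the CVs were obtained. This weakens the size of the loss but not the ratios in step 2, because the same cancellation applied to both measures leaves them unchanged.

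Finally, the article is condensed, and a pooled thickness may be planned elsewhere. But the pooled measures are not left open here: the formula is written out and applied to volume four times.

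**Conclusion.** The point holds as one of efficiency and consistency for the additional pooled measures. They are defined on volume only, while thickness is the outcome named in the heading and used for sizing. By the article's CVs, pooled volume has about 1.6 (medial), 1.5 (femoral) and 1.3 (tibial) times the error SD of pooled thickness, and the lateral combination gains nothing from a change.

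The direction is firm. The power cost is not: it depends on how the CVs were obtained, how much error cancels in paired reading, what the 2.7% contains, and whether the per cent effect is the same on volume and thickness. The last of these was assumed and not varied. Across the scenarios shown, the loss is about 9 to 31 points medial, 6 to 21 femoral and 4 to 15 tibial. The target of 63 and the plate-level thickness tests are untouched.

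**What to change.** In the text after Figure 2, add a combined thickness for the total tibial, total femoral, medial and lateral combinations. Define each as the bone-area-weighted mean of plate mean thickness over total subchondral bone area, with the weights fixed at each woman's baseline bone areas for both scans. Name it the lead combined measure before unblinded results are seen, and keep reporting the four stated volume measures alongside as supportive.

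All inputs are existing software outputs, so no scan needs re-reading. The cost is four more derived variables. Because recruitment has ended and results are awaited, the change must also be dated and documented as made before unblinding, so that it does not look like outcome switching. Keeping the volume results in the report helps with this and preserves comparison with studies that report volume.
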